### Control group

The control group will receive standard geriatric rehabilitation. Routine geriatric rehabilitation in post-acute centers in Catalonia is homogeneous in terms of process and outcome indicators and general staff/patients ratios are marked by the Department of Health [29]. Standard geriatric rehabilitation includes a multidisciplinary and individualized rehabilitation plan, which incorporates physiotherapy, occupational therapy and speech therapy. This plan is established after a comprehensive multidisciplinary geriatric assessment, and shared through the electronic health records.

### Outcome assessments

All outcome assessments will be performed by trained physiotherapists, certified to use the Functional Independence Measure (FIM) and blinded to treatment allocation. Table 2 summarizes assessment tools administered in this study and the specific assessment time periods of each one. We will monitor and record whether group allocation is revealed during the outcome assessment.

**Table 2 Tab2:**
[figure not shown]
Schedule of enrolment, interventions, and assessments for the IMAGINE study

#### Primary outcome measures

Functional Independence Measure (FIM), validated for use in stroke survivors [30], is a sensitive and comprehensive tool to assess the level of independence in basic activities of daily living, which is considered the golden standard for stroke rehabilitation. The scale includes 18 items, grouped into 2 subscales: 1) motor and 2) cognition. Each item is scored on a 7-point ordinal scale (1–7, higher values indicating more independence). Combined motor (13–91 points) and cognitive (5–35 points) subscale scores provide the total score (18–126 points; higher values indicating more independence). In this study, a version translated into Spanish was administered.

#### Secondary outcome measures

Complementary measures of function/disability. The Modified-Rankin Scale (m-RS) is a short measure of disability and dependence, routinely used for 3 months clinical follow-up, and rated in an ordinal scale with 6 categories ranging from zero (no symptoms) to five (complete physical dependence). A seventh category can be added to signify death [31]. In this study, a version translated into Spanish was administered.In-hospital physical activity will be measured once through accelerometers, placing ActivPAL® devices on the preserved leg during 7 consecutive in-hospital days, to measure mainly time spent sitting and standing. This device has been validated in post-acute stroke samples [32, 33].Physical performance improvement will be measured using the Spanish validated version of the Short Physical Performance Battery (SPPB) (0–12 points, worse–best), which includes sub-tests of balance, strength and gait speed [34].Adverse events registration will include: falls, fractures, cranial traumatism, pain (Visual Analogue Scale from 0 to 10 points), cardiovascular events (angina, myocardial infarction, TIA, stroke), aspiration pneumonia/respiratory infections, readmissions to acute hospitals and death.General Self-Efficacy scale [35] is a 10-item tool designed to assess optimistic self-beliefs to cope with a variety of difficult demands in life. This scale is directly correlated to emotion, optimism and work satisfaction. The total score ranges between 10 and 40, with a higher score indicating more self-efficacy. Negative correlations are found with depression, stress, health complaints, burnout, and anxiety.Montreal Cognitive Assessment (MOCA) [36] is a brief instrument recommended for cognitive impairment (CI) screening in people who have suffered a stroke or TIA. It is sensitive to changes in acute temporary CI after mild stroke/TIA [37]. The test assesses visuospatial abilities, short-term memory, executive functions, language and fluency, abstraction thinking, orientation, attention, concentration, and working memory. The scale includes 10 questions (total score range 0–30). Higher scores indicate higher cognitive performance.Mental health: Depressive symptoms by means of the Yesavage Geriatric Depression Scale (GDS) 15 items (0–15 points; worse – best) [38] and the mental wellbeing with the Warwick-Edinburgh Mental Well-being Scale (WEMWBS), which includes 14 questions with answers coded from 1 ‘Never’ to 5 ‘Always’ (14–70 points, worst – best) [39].Duke Social Support Index 11 items (DUKE-UNK-11) will be used to assess social support and effective social contacts during the rehabilitation process, effective caregiver at home, and perceived social support (11–55 points; lower – higher social support) [40].Care results. We will collect data on length of stay (days), discharge destination (home, nursing home, long-term care, acute hospital, death), and hours of rehabilitation.Participation in leisure activities during admission and after-discharge, reported by nurses, stroke survivors and / or caregivers, will be collected.Rehabilitation efficiency. Scores will be computed in terms of improvement of FIM/length of stay.Quality of life. A generic measure of quality of life will be obtained using the EQ-5D-5L tool, which includes two components. A health state description comprises 5 items assessing the dimensions of mobility, self-care, usual activities, pain/discomfort, and anxiety/depression and evaluation, via categorical questions. An evaluation part using a Visual Analogues Scale for retrieving from respondents an overall judgment on their health in a scale from 0 to 100 [41, 42].

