### Randomization and blinding

After inclusion in the study and obtaining informed consent, participants will be randomized centrally to intervention or control group in a concealed allocation manner. That means that, in each study site, a researcher not involved in the assessments will access the OxMaR minimization software through a secure web access [25], and obtain the participant’s random treatment allocation. Randomization will be based on the minimization method, which has proven to provide balanced allocation of study participants in small trials, with respect to prognostic participant characteristics [26]. For each participant, treatment allocation will partially depend on the characteristics of the already enrolled participants [25]. The prognostic factors included in the minimization algorithm are: study site, gender (male or female), and type of stroke (ischemic or hemorrhagic). Due to the nature of the intervention, participants cannot be blinded to allocation, but will be strongly advised not to disclose their allocation status at any assessments. The assessments will be conducted by a healthcare professional (physiotherapist) blinded to treatment allocation. The assessors are encouraged to maintain the blind as far as possible, nonetheless, the assessor must report if the participant allocation was revealed.

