**Fig. 1 Fig1:**
[figure not shown]
Logic model of IMAGINE project

MI will be provided at the hospital ward, either in the person’s room or in an office nearby, according to their preferences and mobility. MI will be structured in four sessions: session 1 will be held one week from admission; session 2 within 6 days after the first session; session 3 at 1 week from the second session; and session 4 will be carried out pre-discharge.

The common goals for all sessions are:
To engage the stoke survivor in his/her care.Collaborative co-creation of a personalized rehabilitation plan, which would complement the routine geriatric rehabilitation.Reinforce engagement and adherence to the plan to maintain behavior change and functional improvement at 3 months.

The emphasis on each of the different goals will vary according to each MI session (see Fig. 2). Although this intervention focuses on physical training and functioning, during the MI sessions people will be also encouraged to perform other recreational, socializing, relaxing or similar activities during hospitalization, always according to individual preferences and objectives.

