**Fig. 2 Fig2:**
[figure not shown]
Structure and main contents of MI sessions

MI involves the use of different core communication skills: 1) to ask open questions; 2) to affirm the person’s particular strengths, abilities, good intentions and efforts; 3) to use reflective listening; 4) to summarize the situation, and 5) to inform and advise with permission, which is useful to help people to reach their own conclusions about the relevance of any information the practitioner provides [20]. Each session will follow a semi-structured format to ensure homogeneity, while allowing tailoring. Content will generally include: 1) Creating engagement with the stroke survivor by exploring his/her preferences, values and goals, as well as his/her knowledge and expectations about stroke rehabilitation and recovery, 2) enhancing motivation by evoking strengths and abilities of the person, 3) follow-up and reinforcement, and 4) adapting the plan to the improved abilities and to home setting. As a practical milestone, during the second session the stroke survivor will establish tailored goals to complement standard rehabilitation, aimed at increasing involvement in self-care and daily living activities. When appropriate, in some cases debriefing with other professionals involved in the rehabilitation (physical therapists, occupational therapist or nursing staff) will be scheduled, to tailor and adjust the rehabilitation plan considering the functional situation. Figure 2 displays the structure of each session and specific criteria to conduct the additional interview between sessions three and four in case of external or internal modulators (which might have undermined the interviews). MI will be delivered by nurses trained through a certified MI course, and additional coaching by a psychiatrist who is a certified MI trainer will be offered to them throughout the intervention period (two group meetings per year and on demand individual sessions). During the study, quality control of the MI sessions using Motivational Interviewing Treatment Integrity (MITI) Code 3.1.1 [28] will be performed through video recording of a random selection of sessions.

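### Leisure participation may be reported by nurses involved in MI, and no common informant is set for the two arms, so this secondary outcome is open to reporting bias that blinded assessors do not prevent

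*Protocol article*

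**What the plan says.** Secondary outcome measures lists leisure participation as follows: "Participation in leisure activities during admission and after-discharge, reported by nurses, stroke survivors and / or caregivers, will be collected". It names no instrument for this item and no order or priority among the three kinds of informant.

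On blinding, Outcome assessments states: "All outcome assessments will be performed by trained physiotherapists, certified to use the Functional Independence Measure (FIM) and blinded to treatment allocation". Randomization and blinding says the same ("The assessments will be conducted by a healthcare professional (physiotherapist) blinded to treatment allocation") and accepts that "participants cannot be blinded to allocation". The Discussion concedes that those who deliver the intervention can hardly be blinded either, and relies on blinded outcome assessors.

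On the intervention, the Intervention section says "MI will be delivered by nurses trained through a certified MI course" and "MI will be provided at the hospital ward". It adds that "during the MI sessions people will be also encouraged to perform other recreational, socializing, relaxing or similar activities during hospitalization". It also allows, in some cases, a debriefing of other professionals, including nursing staff, to adjust the participant's plan.

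**The concern.** The outcome is something the MI sessions try to change, and one permitted source of the data is the professional group that delivers those sessions. A nurse who has agreed leisure goals with a participant, or has been briefed on them, knows the allocation and may be more likely to notice and report such activity. Controls have no corresponding contact. Because the informant is left open, the mix of nurse, participant and caregiver reports may also differ between arms.

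The stake is the interpretation of this one outcome. If the MI arm shows more leisure participation, the trial could not separate a change in behaviour from a change in reporting. Later analysis could at most stratify or adjust by informant, and only if informant type had been recorded. It could not remove what a nurse knew when reporting. The accelerometer gives no cross-check, because it is worn once, for 7 in-hospital days, and measures mainly sitting and standing time.

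**Working it through.** **Reading the sections together**

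1. Who may report: nurses, participants, caregivers, or any combination (Secondary outcome measures).
2. Who delivers MI and where: nurses, on the ward (Intervention).
3. What the sessions encourage: recreational and social activity during the stay (Intervention), which the in-hospital part of the outcome records.
4. Who else may know the plan: nursing staff debriefed in some cases (Intervention).
5. What the safeguard covers: the person performing the assessment (Randomization and blinding; Outcome assessments; Discussion). It does not cover the person supplying the content.
6. What would close the gap: a rule excluding the nurses in steps 2 and 4, or fixing the informant. The article contains neither.

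The text therefore permits an allocation-aware informant with a part in the intervention, in one arm only.

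**The plan's own figure**

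The article gives no figure for leisure participation. Its only sample size is for FIM: difference 10, SD 27.9, two-sided alpha 0.05, power 0.80, 10% drop-out.

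- n per arm = 2 × [27.9 × (1.9600 + 0.8416) / 10]² = 122.19
- 122.19 / 0.90 = 135.8, so 136 per arm, as stated.

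This point does not dispute that figure. It is used only for the evaluable number: 136 × 0.90 = 122.4, taken as 122 per arm.

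**Illustration of size (assumed inputs)**

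Assume no true effect, a two-sided 5% test, and an average reporting shift of b standard deviations in the MI arm. With δ = b / √(2/122) = b / 0.1280, the rejection probability is Φ(δ − 1.96) + Φ(−δ − 1.96).

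| Assumed shift b | δ | False-positive probability |
|---|---|---|
| 0 | 0 | 0.050 |
| 0.1 | 0.781 | 0.122 |
| 0.2 | 1.562 | 0.346 |
| 0.3 | 2.343 | 0.649 |

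If the outcome were coded yes/no with 40% recorded participation in truth in both arms (also assumed), the standard error is about 0.063. Shifts of 5, 10 and 15 percentage points then give about 12%, 35% and 66%.

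In both cases the shift is an average over the whole MI arm. If only a fraction f of MI-arm records came from involved nurses, and those were shifted by s, the arm-level shift would be f × s. With f = 0.5 and s = 0.2 SD it is 0.1 SD, and the false-positive probability is about 12%. The documents give neither f nor s.

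**The case against.** The other side has substantial points.

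- **Blinding rule.** A reader might infer that the leisure item contradicts the statement that blinded physiotherapists perform all assessments. The text does not establish that. One sentence says who performs the assessment and the other says whose report is used, and a blinded physiotherapist can record what an informant says. The self-reported scales in this trial also rest on participants who know their allocation. What stands is narrower: the safeguard does not reach the content of a nurse's report.
- **Who the nurses are.** A reader might infer that the MI interviewer is the reporter, that controls often lack a nurse informant, or that nurses will over-report. None of this is stated. Controls are inpatients in the same units, and nurses who see both arms could report on both. These are possibilities that the text leaves open.
- **Open choice of informant.** The wording may simply reflect two settings, with nurses observing during the stay and participants or caregivers reporting afterwards. The informant would then vary by period, equally in both arms. That is a fair reading, but the article does not require it.
- **Material not shown.** The schedule table is missing from the text at hand, and the article condenses a fuller protocol that may set the informant per visit. The absence of a form or visit-level detail is therefore not counted here. What counts is that the rule the article does state admits nurses without restriction.
- **Self-report is no cure.** MI participants know their allocation and were personally encouraged in these activities, so their reports may also be biased. This is correct, and it is why replacing every nurse report with self-report is a debatable trade. It does not justify keeping involved nurses as informants.
- **Importance.** Leisure participation is in neither the secondary objectives of the Abstract nor the hypotheses in the Background. This limits the weight of the point.

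**Conclusion.** The point holds as a permitted and avoidable risk. As written, the plan lets nurses who deliver MI, or who have been debriefed on an MI plan, report an outcome that MI encourages, and it does not require the same informant in both arms. The outcome may therefore carry differential reporting bias that blinded assessment does not prevent.

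The documents do not show that such bias is present, and its size cannot be derived from them. The 12% to 65% range is arithmetic on assumed shifts and shows only that modest differential reporting could matter at this sample size. The consequence is confined to this secondary outcome. The FIM analysis and the sample size of 136 per arm are unaffected.

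**What to change.** Amend the leisure item in Secondary outcome measures as follows:

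1. State that nurses who deliver MI, and nurses debriefed on an MI participant's plan, may not be informants for this outcome.
2. Set one informant order per period, identical in both arms; for example, the participant first and the caregiver only when the participant cannot answer.
3. Have the blinded assessor put the same fixed questions at the existing 30-day/discharge and 3-month assessments.
4. Record informant type for every report, compare it by arm, and report the outcome as based on unblinded informants.
5. Keep MI nurses' observations of leisure activity in the process evaluation, where the interviewer's session records already sit.

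The cost is a wording change, a few questions at existing contacts and one extra data field. The minimum telephone set in Procedure does not name leisure participation, so the questions would have to be added there for 3-month assessments done by telephone. The downsides are that some ward observation is lost, which matters most for participants with poor recall, and that participant self-report remains unblinded.

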
#### Covariates assessed at admission

Socio-demographic variables: age, gender, civil and marital status.Clinical data: Stroke characteristics (ischemic/hemorrhagic, Oxfordshire CSPC, acute treatment, etiology) clinical variables such as chronic diseases and comorbidity measured by a Spanish translated version of the Charlson index [43] will be collected. In addition, type and number of pharmacological treatment, nutritional status with the Spanish validated version of the Mini Nutritional Assessment-Short form (MNA-sf) [44].

### Procedure

Table 2 depicts full procedures of the project.

In case of discharge before 30 days, the follow-up assessment will be performed the day of discharge, always registering the date of the assessment. In case of unplanned discharge (e.g. to emergency/acute hospital), we will collect at least routine available data collected in the rehabilitation unit and administrative data. The 3 months assessment will be performed either at an outpatient’s clinic or at the participant’s home. If face-to-face follow-up is not possible, a telephone assessment can be conducted. In all cases, assessment will include at least the telephone version of: Barthel, Rankin, Lawton, FIM, FAC, GSE, DUKE-UNK-11, GDS-15, EQ-5D.

### Process evaluation

Since MI intervention is a complex intervention, as observed in Fig. 1 (logic model), the trial includes a process evaluation to enhance the interpretation of the results of effectiveness. This is based on the Medical Research Council (MRC) guidance [45, 46], and focuses on how the context, implementation and impact mechanisms might influence each other and shape outcomes. Specifically, we will assess: 1) the quantity and quality of what is delivered (implementation); 2) the generalizability of the effectiveness by understanding the role of context and the comparability between intervention sites; 3) the mechanisms of impact; and 4) perceived impacts and adverse events.

Each assessment will be addressed complementarily by quantitative and qualitative methodological procedures. Observation checklists and attendance registry will be conducted after each MI session by the interviewer. These procedures will collect information on fidelity (achievement of goals and tasks of each session), dose and adverse events. Standardized scales (i.e. self-efficacy) will be included in the baseline, post-intervention and follow-up assessments to explore mechanisms of impact according to the logic model. Contextual characteristics will be collected in a semi-structured questionnaire to capture shared and specific features of each intervention site.

Complementarily, a qualitative evaluation will be used to explore participant experiences with the implementation of the intervention, their personal and social context, the mechanisms of impact and their perceived effects as well as unexpected events. It will consist in in-depth interviews at 30 days and at 3 months on a purposeful sample of participants, selected to maximize variability by gender, disability levels, socio-economic levels, and social support. In addition, a purposeful sample of caregivers and professionals who performed the intervention will be also interviewed. Finally, a focus group with reference rehabilitation professionals of the units will be conducted in each intervention site.

The process evaluation will be done by a MD and a social worker with great experience in qualitative analysis, designing complex evaluations and process evaluation. These professionals will not have another role in this project. The results will be reported at completion.

### Sample size calculation & statistical analysis

Sample size calculation is based on the results of previous RCTs assessing the effect of geriatric rehabilitation on improvement of the FIM. Accordingly, it is expected that geriatric rehabilitation will induce a 20 points improvement in FIM between admission and discharge [47]. This change has been established as “minimal clinically meaningful” improvement [48]. It is expected that MI plus geriatric rehabilitation will result in a “moderately relevant” clinical improvement in FIM, estimated to be 30 points. That is, MI will induce an additional improvement of 10 points (which corresponds to approximately 10% of total FIM score), compared to the control group. Considering a common standard deviation of 27.9 points in FIM, a 10% of drop-out rate at 30 days, and accepting an alfa risk of 0.05 and a beta risk of 0.2 in a bilateral contrast, we would need to include 136 stroke survivors in each branch (total sample = 272) to detect this improvement as statistically significant. Calculations were obtained using the GRANMO program [49].

Descriptive statistics will be presented for the overall characteristics of the study sample (intervention and control group) as frequencies and percentages for nominal or categorical variables and means and standard deviations for continuous ones. Baseline comparisons between treatment groups will be assessed as t-tests and chi-square tests, to check for potential imbalances in group composition and characteristics.

The effect of MI in the change in total FIM score between baseline and follow up (30 days) will be explored through a longitudinal repeated-measures mixed effects linear model, with the total FIM score as dependent variable, and a 2-level fixed factor accounting for the treatment group (MI or control). The model will adjust for clinically relevant covariates, such as age, gender and the amount of physical activity.

Group analyses will be carried out on an intention-to-treat principle. Missing data will be replaced by multiple imputations, after conducting explorations of the possible missingness mechanisms.

Cost-utility analysis will be also performed to compare the benefit and costs of a MI programs. Cost-utility will be measured as the ratio between direct costs (workforce time use to deliver the MI intervention and the related training and supervision, supplementary tests, use of other hospital resources, medical visits, readmissions, treatments, ambulatory rehabilitation, etc.) during hospitalization and also post-discharge (at 3 months) and Quality Adjusted Life Years (QALYs). QALYs will be derived using the EQoL-5D before and after the treatment and at 3 months. Therefore, cost-utility will be calculated as the incremental ratio in € for 1 QALYs in the intervention vs. control group [50, 51].

All analyses will be carried out in Stata 15 (StataCorp. 2017. *Stata Statistical Software: Release 15*. College Station, TX: StataCorp LLC).

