## Abstract

**Background:**

Rehabilitation pathways are crucial to reduce stroke-related disability. Motivational Interviewing (MI), as a person-centered complex intervention, aimed to empower and motivate, and could be a resource to improve rehabilitation outcomes for older stroke survivors. The IMAGINE project aims to assess the impact of MI, as a complement to standard geriatric rehabilitation, on functional improvement at 30 days after admission, compared to standard geriatric rehabilitation alone, in persons admitted to geriatric rehabilitation after a stroke. Secondary objectives include assessing the impact of MI on physical activity and performance, self-efficacy, safety, cost-utility, participants’ experiences and functional status at 3 months.

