The IMAGINE study aims to investigate the effects of enriching usual geriatric rehabilitation with an adapted MI approach on different outcomes related to functional and clinical impact, persons’ satisfaction during hospitalization and cost-utility. We expect that the IMAGINE study will add a relevant contribution for the implementation of this intervention in older stroke survivors needing rehabilitation. Accordingly, this study should inform practice and policy makers on how to move forward towards shared decision making and shared responsibilities in a vulnerable population such as older stroke survivors [24]. With these aims, several hypothesis have been put forward:
MI, conducted during in-patient geriatric rehabilitation with older stroke survivors will result in an improvement in functional status at 30 days and 3 months, compared to standard geriatric rehabilitation alone.The MI intervention will induce a statistically and clinically significant increase in physical activity during the stay in the geriatric rehabilitation department, and an improvement in physical performance, compared to controls.The increase in physical activity and performance will be dose-correlated with the improvements in functional status.The intervention will result in a more favorable and satisfying experience with care during hospitalization for the participants, caregivers and professionals involved.Participants will increase their self-efficacy.The intervention will be a cost-effective strategy to improve participant outcomes at an acceptable cost (or even with no relevant incremental costs).The intervention will be safe for the stroke survivors. An increased number of adverse events potentially associated to geriatric rehabilitation and exercise will not be observed in the intervention group compared to control group

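### The primary FIM model adjusts for the amount of physical activity, which is probably measured after randomisation and which MI is meant to raise; this can bias the total effect of MI

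*Protocol article*

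**What the plan says.** In Sample size calculation & statistical analysis, the primary analysis is introduced as follows: "The effect of MI in the change in total FIM score between baseline and follow up (30 days) will be explored through a longitudinal". The method is a linear mixed model for repeated measurements, in which total FIM is the response and treatment group is a factor with two levels. The covariate sentence is: "The model will adjust for clinically relevant covariates, such as age, gender and the amount of physical activity". It does not say whether activity means activity before the stroke, at admission or during the stay. The same section calls the group analyses intention-to-treat and bases the sample size on a 10-point FIM difference.

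Elsewhere the article treats activity as something MI should change:

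- Abstract: "Secondary objectives include assessing the impact of MI on physical activity and performance".
- Background, second hypothesis: "The MI intervention will induce a statistically and clinically significant increase in physical activity during the stay in the geriatric rehabilitation department".
- Background, third hypothesis: "The increase in physical activity and performance will be dose-correlated with the improvements in functional status".
- Secondary outcome measures: "In-hospital physical activity will be measured once through accelerometers", worn for seven consecutive days in hospital.

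The section on covariates assessed at admission lists socio-demographic items ("Socio-demographic variables: age, gender, civil and marital status"), stroke and comorbidity data, drug treatment and nutritional status. Physical activity is not among them.

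**The concern.** The second hypothesis draws an arrow from MI to activity, and the third links activity to function. A variable between treatment and outcome is a mediator. If it enters the primary model, the treatment coefficient no longer answers the stated question, which is what adding MI to usual rehabilitation does to FIM at 30 days. At best it answers what MI does apart from any change in activity.

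There is a second route to bias. Stroke severity or frailty can plausibly affect both how much a patient moves and how well the patient recovers. Conditioning on activity that MI has changed then links treatment group to those causes and undoes part of the balance that randomisation gave. This does not require that activity itself improves FIM.

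At stake is the primary estimate. A trial in which MI works as its designers expect could report a weakened effect because the model adjusts part of it away.

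**Working it through.** **1. The planned sample size.** Inputs from the sample size paragraph: difference 10, SD 27.9, two-sided alpha 0.05, power 80%, drop-out 10%.

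n per arm = 2 × [27.9 × (1.960 + 0.842) / 10]² = 122.2. Dividing by 0.9 gives 135.8, so 136. The stated 136 per arm is reproduced. It is powered for the whole 10-point effect.

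**2. Is activity post-randomisation?** Participants are randomised after consent (Randomization and blinding). The recording is made on the ward and serves as an outcome of MI. On timing, the Intervention section states: "session 1 will be held one week from admission". A recording completed before that session would not be affected by MI, but it could not show that MI raises activity either. The outcome role therefore points to a recording made at least partly after MI starts. Table 2, which holds the schedule, is not shown, so this is probable and not certain.

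**3. What adjustment does under different codings.** The coding was checked by simulation: 122 evaluable per arm (136 × 0.9 = 122.4), true total effect 10, FIM SD 27.9, baseline to 30-day correlation 0.6, complete data, no shared cause. MI shifts activity by 0.5 SD. The correlation, the shift and the mediated share of 50% are assumptions. Mean estimates over 2,000 replicates:

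| Coding | Without activity | With activity |
|---|---|---|
| 30-day FIM adjusted for baseline FIM | 10.1 | 5.0 |
| Group-by-time contrast, activity as main effect | 10.1 | 10.1 |
| Group-by-time contrast, activity-by-time term added | 10.1 | 5.1 |
| Group main effect only, no interaction | 5.0 | 2.5 |

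In the second row a value that is constant within a patient shifts both time points equally and cancels from the change. In the last row the coefficient averages the baseline and 30-day group differences, so it is already half the effect before activity enters. That is a separate matter from this point.

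**4. Size where the adjustment bites.** For the first and third codings the target becomes 10 × (1 − m), where m is the mediated share. The documents give no m, so a range is shown. Power is from a two-sample t test with 122 per arm and SD 27.9; standard error = 27.9 × √(2/122) = 3.57.

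| m (assumed) | Points left | Power |
|---|---|---|
| 0% | 10 | 79.6% |
| 30% | 7 | 49.7% |
| 50% | 5 | 28.6% |
| 70% | 3 | 13.3% |

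The SD is held at the planning value. Baseline or activity adjustment would usually lower the residual SD, so these powers are on the plan's own scale and do not forecast the fitted model.

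**5. Departures from the simple case.** These were simulated (4,000 replicates) in a single-time-point linear model. At m = 50%, activity measured with reliability 0.7 leaves 6.5 points, because an error-prone mediator is only partly removed. A shared unmeasured cause with loading 0.4 on both activity and FIM leaves 2.8 points. With the same shared cause and no mediation at all, the coefficient is 7.7 where the truth is 10.

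**The case against.** The strongest reply concerns the model. The plan names a repeated-measures model for change in FIM, and the usual treatment effect there is the group-by-time term. Activity is measured once, so as a main effect it drops out of that contrast. This is correct. A reader might infer that the plan as written will turn 10 points into 7, 5 or 3. The documents do not support that: it needs another coding and an assumed mediated share. What does not follow is that the plan is safe. The article names only a two-level group factor and no interaction, so nothing fixes the harmless coding, and under that coding the adjustment contributes nothing to the contrast.

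The second reply is that the covariate may be a different, baseline measure of activity. A reader might infer that the plan contradicts itself whichever way the recording is timed. That is too strong. Table 2 is not shown, and the Procedure section names instruments (Barthel, Lawton, FAC) that the outcome and covariate sections do not describe as study measures, so the text is not a full list. A separate admission or pre-stroke activity item beside the accelerometer outcome would remove the conflict. The article mentions none.

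Third, the covariates are given only as examples, and an analysis plan may settle them. That is fair for what is left open. Activity, however, is one of three covariates actually named, and an analysis plan that follows the text takes the problem over.

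**Conclusion.** The concern holds in a limited form. The text places in the primary model a variable that is probably a post-randomisation mediator on the article's own hypotheses, and conditioning on it can bias the total effect of MI. Bias toward no effect is the likely direction if MI raises activity and activity helps function, or if a shared cause raises both; it is not guaranteed.

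The size cannot be derived from the documents. It ranges from nothing, under a group-by-time contrast with complete data and activity as a main effect only, to a loss equal to the mediated share under the codings where the adjustment bites. That exact loss assumes linearity, activity measured without error and no unmeasured common cause. No coding examined makes the adjustment useful for the total effect. The sample size of 136 per arm is not in question.

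**What to change.** In the primary model, replace the reference to the amount of physical activity with a statement that only variables measured before randomisation may be covariates. Examples already in the protocol are age and the minimisation factors (site, gender, stroke type). Handle baseline FIM either as the baseline response in the repeated-measures model or as a covariate, not both. If a baseline or pre-stroke activity measure was intended, name it and say when it is taken.

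Keep the accelerometer recording as a secondary outcome. Examine the third hypothesis in a separate mediation analysis, which also suits the process evaluation's aim of studying mechanisms of impact.

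The cost is a sentence or two of analysis wording, best settled before unblinded data are seen. It needs no new data or visits and no change to the sample size.
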